## Abstract

**Background:**

Cancer survivors frequently develop cognitive impairment, which negatively affects their quality of life and emotional well-being. This study compares the effectiveness of a well-established treatment (neuropsychological treatment) with the Unified Protocol for Transdiagnostic Treatment of Emotional Disorders (UP) to reduce these cognitive deficits and evaluate the effect of both treatments on anxiety-depressive symptoms and the quality of life of cancer survivors.

**Methods:**

A three-arm, randomized superiority clinical trial with a pre-post and repeated follow-up measures intergroup design using a 1:1:1 allocation ratio will be performed. One hundred and twenty-three cancer survivors with mild to moderate cognitive impairment will be randomly assigned to one of the study interventions: a cognitive rehabilitation intervention group, an intervention group with UP intervention, or a control group on the waiting list. The primary outcome is to observe a significant improvement in cognitive function in both intervention groups and a significant decrease in emotional impairments in comparison with the waitlist group. Improvements in anxiety, depression, and quality of life are also expected as secondary outcomes. These results will be maintained at 6 months of follow-up.

**Discussion:**

The aim of this trial is to test the efficacy of the UP intervention in reducing cognitive deficits in breast cancer survivors. The results of this trial may be useful in reducing the presence of cognitive problems in cancer survivors and improving their emotional state and quality of life.

**Trial registration:**

ClinicalTrials.gov NCT05289258. Registered 12 March 2022, v01.

**Supplementary Information:**

The online version contains supplementary material available at 10.1186/s13063-022-06731-w.

## Administrative information

Note: the numbers in curly brackets in this protocol refer to SPIRIT checklist item numbers. The order of the items has been modified to group similar items (see http://www.equator-network.org/reporting-guidelines/spirit-2013-statement-defining-standard-protocol-items-for-clinical-trials/).

## Introduction

### Background and rationale {6a}

Breast cancer remains a major health problem worldwide. In 2020, an estimated 2.3 million women were diagnosed with breast cancer and there were 685,000 breast cancer-related deaths globally. With a 5-year prevalence of 7.8 million cases, breast cancer is the most common cancer worldwide. Despite this, advances in treatment and prevention have led to breast cancer survival rates of up to 90%, especially in cancers diagnosed at an early stage [1]. In Spain, a similar pattern can be observed, with breast cancer being one of the most frequently diagnosed types of cancer. In 2020, there were 6651 cases of breast cancer-associated mortality in the country, and it is estimated that the incidence of breast cancer will be 34,750 cases in 2022 [2].

Alterations in cognitive functioning are frequently observed in patients who undergo chemotherapy as treatment for noncentral nervous system cancer. Previous systematic reviews have estimated that up to 75% of patients showed a cognitive decline after chemotherapy, particularly in the domains of memory, executive function, attention, concentration, and processing speed. These symptoms negatively impact on patients’ quality of life, including impairments in terms of autonomy, self-confidence, social relationships, and return to work or education [3–5]. These alterations in cognitive functioning are usually mild to moderate and frequently appear after chemotherapy. However, the persistence of these symptoms varies over time. For example, according to several studies, 15–35% of patients report experiencing changes in their cognitive functioning months after the end of treatment [3]. In breast cancer patients, these alterations are observed to appear after chemotherapy and continue to be present 1, 5, and even 20 years after treatment [4]. In this line, Wefel et al. [6] found that 71% of breast cancer patients showed cognitive impairment after chemotherapy, and 61% of patients showed cognitive impairment 6 months after completing treatment. These results are similar to those of Collins et al. [7], who observed cognitive impairment in 48% of breast cancer patients and found that more than a third continued to show this impairment 1 year after treatment. Despite these results, few studies have examined the long-term cognitive decline in patients, although evidence suggests an improvement in cognitive decline after 6 months of chemotherapy completion [5].

Several types of interventions, from pharmacological treatment to physical activity, have been developed to reduce cognitive impairment in cancer patients [3]. Among psychological interventions, cognitive behavioral therapy and cognitive training have shown positive results, although studies on these interventions have been carried out with limited samples of patients or without a control group [8–12]. However, since both anxiety and depression are related to cognitive impairment in cancer patients, a transdiagnostic intervention such as the Unified Protocol (UP) may be effective in reducing the presence of symptoms of cognitive impairment in these patients [13–16].

Therefore, the primary objective of this trial is to test the efficacy of the UP in reducing cognitive decline and improving the emotional well-being (anxiety and depression) and quality of life of patients. The secondary objective is to establish the efficacy of neuropsychological treatment to reduce cognitive impairment and improve the psychological well-being and quality of life in these patients

### Objectives {7}

The following research hypotheses have been formulated:The UP will be more effective in reducing cognitive impairment, symptoms of anxiety, depression, and quality of life than the neuropsychological treatment at post-treatment and follow-up (6 months).Patients in the UP and in the neuropsychological treatment group will obtain better scores in cognitive impairment and symptoms of anxiety, depression, and quality of life than those in the waitlist group at post-treatment and follow-up (6 months).

### Trial design {8}

This is the protocol of a three-arm, controlled, randomized superiority trial, with a pre-post and repeated follow-up measures intergroup design. Participants with mild to moderate cognitive impairment will be randomly assigned to group 1: Unified Protocol for Transdiagnostic Treatment of Emotional Disorders (UP) intervention, group 2: Neuropsychological intervention, or group 3: Waitlist control group. For ethical reasons, the participants in group 3 will be offered the option to receive the neuropsychological intervention. The evaluation will be carried out at three time points: an initial evaluation prior to randomization (pre-treatment; T0), at the end of the intervention (post-treatment; T1), and at 6 months after completing the intervention (T2) (see Fig. 1).

**Fig. 1 Fig1:**
[figure not shown]
Study protocol flowchart

## Methods: Participants, interventions, and outcomes

### Study setting {9}

This clinical trial will be conducted at the Reina Sofía University Hospital of Cordoba, Spain, and at the Faculty of Medicine of the University of Cordoba, Spain. The Reina Sofía University Hospital provides patients integral care, including diagnosis, cancer staging, specific oncological treatment, continuous care, palliative care, and disease follow-up care. The research group is responsible for the study design, the training of the personnel involved in the data collection, the application of the interventions, the provision and preparation of all study documents, the supervision of the study, the treatment and analysis of the data obtained, and to communicate and disseminate the research results.

### Eligibility criteria {10}

Inclusion criteria in the trial: Men and women aged 18 to 70 years. Cancer diagnosis, stages I-III. Cancer type: Breast. The participants must have received the last chemotherapy session in the last 6 months and completed a maximum of 6 years of treatment. Probable or mild to moderate cognitive impairment (score of 10–26 points on the Mini-Mental State Exam [MMSE]). Fluent in Spanish. Not currently participating in another clinical trial. Not currently receiving other psychological treatment.

Exclusion criteria in the trial: Men and women aged > 70 years. Diagnosis of stage IV cancer or other types of cancer. Last chemotherapy session < 6 months or > 6 years. No cognitive impairment (MMSE score of 27–30 points). Diagnosis of mental disorder (including substance abuse) prior to cancer diagnosis. Disease relapse after completion of chemotherapy treatment. Diagnosis of neurodevelopmental disorder. Diagnosis of diseases that affect cognitive performance such as hypertension, cardiac diseases, epilepsy, dementias, multiple sclerosis, functional disorders (chronic fatigue syndrome, irritable bowel syndrome, post-concussion syndrome, whiplash syndrome), central nervous system (CNS) infections (HIV, encephalitis), metabolic disorders (diabetes, B12 deficiency), obstructive sleep apnea, brain damage (stroke, traumatic brain injury, CNS cancer). Use of medications/substances that interfere with cognitive function such as pregabalin, gabapentin, topiramate, antidepressants tricyclics, sodium valproate, anticholinergics, methylphenidate, or typical antipsychotics

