### Recruitment {15}

The oncology team at the Reina Sofia University Hospital of Cordoba (Spain) will be responsible for assessing the suitability of the patients to enter into the study during their routine visits, based on their clinical histories and following the inclusion and exclusion criteria. Eligible participants will be contacted using a telephone by a member of the research team with formation in clinical psychology to provide an invitation to participate in the study. It is expected that a sufficient number of participants will be recruited to start the different interventions with the same number of participants at the same time.

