## Assignment of interventions: allocation

### Sequence generation {16a}

Participants who obtain scores indicating mild or moderate cognitive deterioration will be randomly assigned to one of the three interventions (Neuropsychological treatment/Unified Protocol for the Transdiagnostic Treatment of Emotional Disorders (UP)/waitlist group) at a 1:1:1 ratio using a computer-generated set of numbers (https://www.randomizer.org/) and stratified by psychiatric medication and fibromyalgia diagnosis (if any).

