## Data collection and management

### Plans for assessment and collection of outcomes {18a}

#### Mini-Mental State Examination (MMSE)

The MMSE consists of a quantitative screening test of cognitive function comprising 11 questions that are administered between 5 and 10 min. Three items are scored from 0 to 5, 3 items are scored from 0 to 3, 1 item is scored from 0 to 2 and 4 items are scored from 0 to 1. The maximum score that can be obtained is 30, with a higher score indicating less cognitive impairment. A score below 24 points indicates possible cognitive impairment. The validity of MMSE has been demonstrated in a Spanish population with a Cronbach’s alpha of .94 [27, 28].

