## Discussion

Cancer patients frequently develop cognitive impairments that negatively affect their quality of life and functional status, especially those who have undergone chemotherapy [3–5]. Several psychological interventions to reduce the frequency of these cognitive alterations have shown positive results. However, a relationship has been observed between emotional well-being (anxiety and depression) and the severity of cognitive alterations in these patients. Therefore, a transdiagnostic intervention can be useful to improve their emotional state and cognitive performance [8–16].

This protocol includes information on a randomized controlled trial in which an intervention based on Barlow’s Unified Protocol (UP) will be carried out with the aim of improving the emotional state and cognitive performance of cancer patients. The UP intervention will be compared to a well-established neuropsychological intervention and a waiting list group. The group assigned to the transdiagnostic intervention group is expected to obtain significantly better outcomes in cognitive performance, anxiety, depression, and quality of life compared to the other two groups.

The planned trial has certain strengths that deserve mention. First, it will include a significant number of participants after estimating the sample size necessary to obtain relevant results. Furthermore, using a randomized controlled trial is an advantage of this protocol, as well as the inclusion of a waitlist control group with which to compare the results. Finally, the intervention based on the transdiagnostic model can help not only to improve the cognitive performance of the participants, but also their emotional state.

Finally, it is necessary to mention some limitations foreseen in this trial. The different treatments which the participants will undergo may influence the results. In addition, differences in the time from completion may influence the participants’ outcomes, although the effect of time on the results is expected to be controlled. Finally, the inclusion of patients with breast cancer only may limit the usefulness of the results, since cognitive alterations appear in cancer patients in general.

Despite these limitations, the expected results of this randomized and controlled trial can help to achieve a comprehensive improvement in cancer patients in relevant areas such as cognitive function and emotional state.

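### The inclusion and exclusion criteria contradict each other on time since chemotherapy and overlap at most at exactly 6 months.

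*Protocol article*

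**What the plan says.** Both criteria stand in the protocol article under Eligibility criteria {10}. The inclusion list says that participants "must have received the last chemotherapy session in the last 6 months and completed a maximum of 6 years of treatment". The exclusion list removes "Last chemotherapy session < 6 months or > 6 years".

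Under Recruitment {15}, the oncology team judges suitability "based on their clinical histories and following the inclusion and exclusion criteria", so a patient has to satisfy both lists.

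The only other remark on the subject is a limitation in the Discussion, that "differences in the time from completion may influence the participants’ outcomes". It gives no bounds. The Demographic Variables Questionnaire names the interval from diagnosis to the end of chemotherapy among its examples, which is a different quantity.

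**The concern.** An inclusion criterion and an exclusion criterion on the same variable should leave a range of patients who pass both. Here they point in opposite directions from the same 6-month mark. The inclusion sentence also attaches the 6-year figure to treatment itself, where the exclusion line attaches it to time since the last session.

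At stake is the definition of the trial population. A trial in people up to 6 months after chemotherapy and a trial in people 6 months to 6 years after it answer different questions about the same interventions. The Background says that evidence suggests cognitive improvement once 6 months have passed since chemotherapy, although it also reports impairment lasting many years. The Outcomes section expects no significant improvement on the waitlist. Both statements are easier to interpret once it is clear which patients are enrolled. If both kinds of patient entered, the sample would be more heterogeneous and the result harder to apply.

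**Working it through.** The protocol gives no figure to reproduce here. The check is an intersection of two intervals.

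**Inputs.** Let *t* be the time from the last chemotherapy session to screening.
- Inclusion sentence: *t* ≤ 6 months.
- Exclusion line: out if *t* < 6 months or *t* > 6 years, so a patient survives it if 6 months ≤ *t* ≤ 6 years (6 × 12 = 72 months).

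**Step 1: apply both.** *t* ≤ 6 and 6 ≤ *t* ≤ 72 (months) gives *t* = 6 only. If the inclusion limit is strict (*t* < 6), the result is empty.

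**Step 2: day counts.** The protocol does not convert months to days, so several conventions were tried, with 6 years taken as 2192 days (an assumption).

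| 6 months taken as | Days passing both, inclusive limit | Days passing both, strict limit | Days surviving the exclusion line alone |
|---|---|---|---|
| 180 days | day 180 only | none | 180 to 2192 |
| 182 days | day 182 only | none | 182 to 2192 |
| 183 days | day 183 only | none | 183 to 2192 |
| 184 days | day 184 only | none | 184 to 2192 |

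The convention makes no difference: at most one day remains.

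**Step 3: the 6-year phrase in the inclusion sentence.** There are two ways to read it.
- As a limit on treatment duration, it says nothing about *t*, and Step 1 is unchanged.
- As a limit on time since treatment, inclusion becomes *t* ≤ 6 months and *t* ≤ 72 months, which is again *t* ≤ 6 months. The phrase then has no function.

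Neither reading removes the conflict.

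**Step 4: what each reading implies at follow-up.** The interventions last 8 weeks (about 2 months) and T2 comes 6 months after they end. If treatment starts soon after screening (an assumption), T2 falls about 2 + 6 = 8 months after entry.
- Inclusion reading: 0 to 6 months at entry, about 8 to 14 months at T2. Essentially every patient passes the 6-month mark while in the trial.
- Exclusion reading: 6 to 72 months at entry, about 14 to 80 months at T2. Every patient has already reached that mark at entry.

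So the two populations differ on the time scale that the Background treats as relevant.

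**The case against.** The strongest reply is that this is a recognizable wording slip. The inclusion sentence carries the same two figures, 6 months and 6 years, as the exclusion line. A 6-year limit is pointless beside a 6-month cap. The other paired criteria (age above 70, stage, cancer type, MMSE) have an exclusion that mirrors the inclusion, and on that pattern the window would run from 6 months to 6 years. The Discussion treats variation in time since completion as a limitation. All of this makes a slip likely. It does not remove the need for correction, because the text never says which list governs and this is an operative threshold.

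Several stronger readings are tempting, and the documents do not support them.
- **That the trial can enrol nobody, or that screeners are applying different windows.** Exactly 6 months can satisfy both lists, and the Trial status section says recruitment has begun. The text shows an ambiguity. It does not show how screening is done in practice.
- **That the comparison between arms is biased.** Allocation is randomized 1:1:1. A mixed population affects precision and applicability and does not by itself create a systematic difference between arms. No sample-size figure depends on the window.
- **That the impairment rates cited in the Background measure the damage.** They do not compare the two windows, so they cannot size the problem.
- **That the MMSE rule is contradictory as well.** Eligibility admits "Probable or mild to moderate cognitive impairment (score of 10–26 points on the Mini-Mental State Exam" and excludes 27–30, which meet without gap or overlap. The allocation section's "Participants who obtain scores indicating mild or moderate cognitive deterioration will be randomly assigned" gives no number and reads as shorthand for passing that screen. The statement "A score below 24 points indicates possible cognitive impairment" describes the instrument and does not say who is enrolled. Scores of 24–26 are eligible.

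**Conclusion.** The point holds as an internal contradiction in the eligibility criteria. The two lists overlap at most at exactly 6 months since the last session, under every day count tried. Taken separately, they select essentially disjoint populations: 0 to 6 months, against 6 months to 6 years. The consequence is an undefined target population, possible added heterogeneity, and uncertainty about whom the result applies to.

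The conclusion rests on the literal wording of two sentences in one section and on the absence of any other statement of the window in the article. It does not rest on any assumption about recovery rates. Which window was intended cannot be established from the document.

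**What to change.** The sponsor should reconcile the two criteria and state the same window in both lists. It should be expressed as time from the last chemotherapy session to screening, with an explicit lower and upper bound and a statement of whether each bound is included. The inclusion phrase about years of treatment should be replaced by that wording. The exclusion line and the repeated 6-year figure suggest that the slip lies in the inclusion sentence, but the sponsor must confirm this.

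Patients enrolled since 25 April 2022 should then be checked against the confirmed window, using the date of the last session in their clinical histories. Any who fall outside it should be documented.

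The cost is a short amendment, which the protocol's own amendment procedure sends to the ethics committee for approval, and a review of the records of patients already enrolled. The sample size and the analysis do not change.

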### Who will take informed consent? {26a}

After recruitment, participants will be arranged to be screened for cognitive impairment using the MMSE and asked to sign the informed consent form. Participants will be provided with information sheets with general information about the study and will be offered the opportunity to ask any questions about their participation. If the participant agrees, he/she will be provided with a written informed consent that will guarantee the confidentiality of the data and the possibility to leave the study at any time without any adverse effects (revocation of informed consent). The informed consent will be collected by a member of the research team with training in clinical psychology.

### Additional consent provisions for collection and use of participant data and biological specimens {26b}

The data obtained will be used only for the purposes of this research and biological samples will not be collected.

## Interventions

### Explanation for the choice of comparators {6b}

This trial tests the efficacy of an adaptation of Barlow's Unified Protocol in reducing the presence of symptoms of cognitive impairment in cancer patients, compared to a cognitive rehabilitation program whose results have been shown to be effective in previous studies. This rehabilitation program includes training in memory and processing speed and has been tested in breast cancer patients treated with chemotherapy in randomized controlled trials, showing significant improvements in patients' cognitive functions after the intervention and at 2 months follow-up. The wait-list control group will be assigned to receive usual care [17–19].

### Intervention description {11a}

Unified Protocol for the Transdiagnostic Treatment of Emotional Disorders (UP). The UP intervention will focus on a deficit in emotional regulation common to all emotional disorders (ED). Specifically, the intervention will address the adaptive value of emotions and promote tolerance to intense emotions as well as identify and modify dysfunctional emotional regulation strategies. Patients will receive 8 group therapy sessions (8–10 cancer survivors per group) with all UP modules [20]. The Spanish version of the therapist’s guide and the patient’s workbook will be used [21]. All patients will receive the workbook to inform them of the contents of each session, aid them in doing the recommended exercises between sessions, and help them once the treatment is completed. The treatment will last 8 weeks (one session per week) as follows:*Session 1: Motivation for change and commitment to treatment.* The main objectives of the first session are to establish the therapeutic relationship and promote motivation for change. Therefore, tasks pursuing that goal will be carried out such as the analysis of the advantages and disadvantages of change and the setting of treatment goals or life goals.*Session 2*: *Understanding emotions.* The second session will focus on teaching the adaptive components of emotions in patients and will begin by working with the concept of emotion-driven behaviors (EDBs), differentiating between three emotional components: behaviors, thoughts, and physical reactions.*Session 3: Emotional awareness training. Learning how to observe experiences.* In this session, patients will be trained in emotional awareness through the practice of exercises focusing on the present without judging what they are perceiving. For example, exercises involving mood induction with music.*Session 4: Cognitive restructuring.* The objective of this session is to promote cognitive flexibility. To achieve this aim, participants will be trained to identify and modify non-adaptive thoughts (e.g., through cognitive restructuring or positive self-instruction).*Session 5: Emotional avoidance and EDBs.* This session will analyze emotional avoidance patterns and EDBs as well as their role in the development and maintenance of emotional disorders. In addition, patients will be trained to modify their dysfunctional behaviors.*Session 6: Physical sensations tolerance.* In this session, the objective is to train patients in improving their tolerance to physical sensations. To this end, participants will learn to identify uncomfortable inner physical sensations associated with emotions using breathing exercises.*Session 7: Situational and interoceptive emotional exposure.* The objective of this session is to expose the patient to emotions by promoting habituation instead of emotional avoidance. A situational and emotional avoidance hierarchy will be developed and followed by exposure exercises for that purpose.*Session 8: Maintenance of treatment gains and relapse prevention.* In the last session, participants will check their progress and what was learned in previous sessions will be recapitulated to promote the later use of this knowledge once the intervention is over. The aim is to provide patients skills to deal with demanding situations in the future.

Neuropsychological treatment consists of a combination of the programs tested by Von ah et al. [17]. These programs involve cognitive training adapted from the Advanced Cognitive Training for Independent and Vital Elderly (ACTIVE) intervention [18] and processing speed training using the InSight program (developed by Posit Science) [19].

The first memory training will consist of teaching the patients memorization techniques for remembering word lists, text material, and sequences. Participants learn how to apply principles of meaningfulness, clustering, organization, visualization, and association using strategies such as visual memory support, story mnemonic, and the method of loci [22]. These tasks will be performed in the first hour of every session. The sessions will be structured as follows: Sessions 1–4 will focus on strategy instruction and exercises to practice the strategy learnt in that session. In sessions 4–8 additional practice exercises to promote self-efficacy in terms of performance will be provided. The second program will consist of a series of exercises on processing speed of varying difficulty. Exercises include time-order judgment, discrimination, spatial-match, forward-span, instruction-following, and narrative-memory tasks. The InSight program automatically adjusts the difficulty of these exercises to users’ performance to maintain an 85% rate of correct performance [19]. In the same line, this program systematically reduces the stimulus duration during a series of progressively more difficult tasks that are displayed on a computer. These exercises will be performed in the second hour of each session throughout the entire intervention.

The intervention will be carried out in groups with a maximum of 5 participants per group [17] and consists of 8 weekly sessions of 2 h each: the first hour for memory training and the second for processing speed exercises (PSE). Contents for 8 weeks:*Session 1: Clustering strategies and PSE.* In the first session, the goal is to learn how to organize a list of verbal or visual stimuli into meaningful categories and clustering during the first hour. To achieve this goal, the psychologist will introduce the session and explain the strategies and exercises to practice them. In the second hour of the session, the participants will be trained in processing speed using the InSight program. The psychologist will remain in the room to answer any questions and support the participants while they do the computerized exercises.*Session 2*: *Summarizing strategies and PSE.* In the first hour of this session, participants will be trained to organize, summarize, and select the main ideas and details in order to remember text-based information. Once the strategies have been explained, paper-based exercises will be used. Later, patients will do processing speed exercises on computers under the psychologist’s supervision.*Session 3*: *Visualizing strategies and PSE.* The first hour of the third session focuses on teaching visualizing strategies to remember different items. In the same line as previous sessions, the strategy will be explained first and the practical exercises will be performed later. The second hour will focus on processing speed exercises using the Posit Science InSight program as well.*Session 4*: *Association strategies and PSE.* In the first hour of this session, the objective is to use association to remember items. In this case, the strategies will be taught using both visual and verbal materials. In the second hour, participants will be trained in processing speed as usual with the psychologist’s support when necessary.*Sessions 5, 6, 7, and 8: Revising strategies and PSE.* In the last four sessions, what was learned in the previous sessions will be entrenched with additional practice exercises in the first hour. Thus, mixed exercises will be done in these sessions where participants are asked to apply different strategies to each exercise and solve doubts. Likewise, processing speed training with the Insight program will be provided in the second hour.

Control group on waiting list. Once the interventions in groups 1 and 2 have been completed, the control group will receive the neuropsychological treatment described above. The group on the waiting list will participate in all the evaluations (T0, T1, and T2)

